### Exploratory efficacy analyses

#### Subgroup analysis

The subgroup analyses will assess differences in intervention effects across pre-specified subgroups (see subheading ‘Covariates and subgroups’). Tests of intervention effect modification will be performed by fitting intervention group and the relevant subgroup main effects and interaction into the models adjusted for baseline scores. Interpretation of evidence of heterogeneity of intervention effects among subgroups will remain exploratory (hypothesis generating) given that the study is not powered to test subgroups in the stratified analysis. Results will be presented as forest plots with *P* values for heterogeneity (interaction test) for each pair of subgroups displayed.

### Sensitivity analysis

A sensitivity analysis of the repeated measures UV dosimeter data will be conducted on the subgroup of participants (*N* = ~ 240) who wear a UV dosimeter at 1 month and 12 months, using GLMMs with random intercepts to account for the repeated measures.

A sensitivity analysis will also be completed comparing the results for people who completed follow-up in the spring/summer of 2018/2019 vs. 2019/2020 due to the bushfires experienced in Australia during the latter period and the potential impact on personal and ambient UV exposure.

A sensitivity analysis will be conducted in which dosimeter data will be used to adjust for the effects of measurement error in the relative-risk estimate for self-reported sun exposure, using established methods [43].

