### Outcome measures

#### Primary outcome measure

The primary outcome for this study is total daily Standard Erythemal Doses (SEDs) measured 12 months after the baseline assessment (baseline questionnaire and UV dosimeter). A SED is an objective measure of UV exposure, measured using a time-stamped electronic dosimeter badge, mounted in light-weight, custom-made wristbands attached to the left wrist (similar to wearing a watch) during daylight hours [16]. UV dosimetry is the gold standard for assessing personal UV exposure [17, 18]. UV dosimeters will be worn by all participants for 10 days at baseline, and again 12 months after baseline. A subgroup of ~ 240 participants will also wear a UV dosimeter 1 month after receipt of the booklet/s. Total daily SEDs will be calculated as the weighted average of the average daily weekday and weekend SEDs (i.e. (weekday× 5 + weekend× 2)/7). SED values will be log-transformed for all analyses.

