### Study variables

Outcomes will be measured at baseline, 1 month after receipt of the booklet/s (except dosimeter outcomes that were only assessed for a subset of participants at 1 month), and again 12 months after baseline as summarised in Table 2. A sample of ~ 240 participants will wear a UV dosimeter for 10 days at follow-up 1 (1 month after receipt of booklet/s).

**Table 2 Tab2:** Schedule of study parameters and collection time points

	Study period				
	Screening/consent	Baseline/randomisation	Intervention delivery	Follow-up^**a**^	
Time point	***-1***	0	***T1***	***F1***	***F2***

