### Primary efficacy analysis

Geometric mean score and 95% CI will also be represented graphically from over time (baseline, follow-ups 1 and 2). The primary analysis will be an intention-to-treat comparison of intervention and control arms for mean differences in UVR exposure measured as log-transformed daily SEDs at 12 months. The primary efficacy of the intervention will be assessed in each phenotypic risk group (high and low). UV dosimeter values will be log-transformed because of their right-skew distribution, and log-transformed values will be interpreted as a percentage change in the geometric mean of SEDs/day [41]. An analysis of covariance (ANCOVA), adjusted for baseline values and all randomised stratification factors will be performed [40]. A sensitivity analysis will be conducted on the subgroup of participants (*N* = ~ 240) that will wear a UV dosimeter for 10 days at follow-up 1 (see subheading 'Sensitivity Analysis'); given the repeated nature of the outcomes in this subgroup, generalised linear mixed models (GLMMs) with random intercepts will be fitted to assess the overall intervention effect. The primary analysis will be based on the complete case principle given that the power was adjusted with a conservative loss to follow-up rate of 15%. However, if 10% or more of the randomised patients do not have their primary outcome recorded, a sensitivity analysis will be performed using multiple imputation methods assuming that data are missing at random.

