### Secondary efficacy analyses

Where outcomes were assessed at three time points (baseline, 1 month, 12 months), including most questionnaire items, data will be analysed using GLMMs with random intercepts for continuous outcome measures, and generalised estimating equations (GEEs) with a log link function for binary outcome measures to estimate relative risks. The GLMM and GEE approach allows us to account for correlation due to repeated measures on each individual [42]. Where outcomes were assessed at two time points only (baseline and 12 months), data will be analysed using ANCOVA for continuous outcome measures [40], and using GLM with log link function for binomial outcome variables to estimate relative risks and 95% CIs. The mean difference and 95% CIs between intervention and control groups at 12 months will be estimated.

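### Two SAP sections define the set for the 1-month dosimeter sensitivity analysis differently, one of them literally requiring 12-month wear, and no 1-month SED contrast is named

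*SAP article*

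**What the plan says.** - **Who is measured and when.** Under Primary outcome measure, "UV dosimeters will be worn by all participants for 10 days at baseline, and again 12 months after baseline". Under Study variables, a sample of about 240 "participants will wear a UV dosimeter for 10 days at follow-up 1 (1 month after receipt of booklet/s"), and the footnote to the schedule table repeats that number for the 1-month visit.
- **First definition of the set.** The Primary efficacy analysis section places the sensitivity analysis in the roughly 240 participants "that will wear a UV dosimeter for 10 days at follow-up 1" and points to the Sensitivity analysis section. Of the model it says that "generalised linear mixed models (GLMMs) with random intercepts will be fitted to assess the overall intervention effect".
- **Second definition of the set.** The Sensitivity analysis section describes the same analysis, with the same N, in those "who wear a UV dosimeter at 1 month and 12 months, using GLMMs with random intercepts to account for the repeated measures".
- **Other uses of 1-month SEDs.** The geometric mean and its confidence interval "will also be represented graphically from over time (baseline, follow-ups 1 and 2"). The Secondary efficacy analyses section has a general mixed-model rule that begins "Where outcomes were assessed at three time points (baseline, 1 month, 12 months), including most questionnaire items"; the only contrast that section names is at 12 months.
- **Aims and principles.** The secondary aims include the effect on short-term outcomes at 1 month. The general considerations put every analysis on an intention-to-treat basis with all randomised participants. The Sample size section allows for up to 15% incomplete follow-up at 12 months.

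**The concern.** The two definitions differ by everyone who has a 1-month record and no 12-month record. A programmer who follows the cross-reference arrives at the narrower one. Applied as written, it makes inclusion depend on something that happens after randomisation and after the 1-month measurement. It therefore sits badly with the all-randomised principle. It also gains nothing: a random-intercept model accepts participants with a single post-baseline value and is valid for them under missing at random, the assumption that the SAP itself adopts. The people dropped would be those whose early SEDs carry some information about later withdrawers, and the complete-case primary analysis does not use those values either.

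A second gap lies beneath this. The short-term effect is a stated aim, but the only inferential model named for 1-month total daily SEDs is directed at an overall effect. An overall effect averages over visits, so it does not answer what happened at 1 month.

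**Working it through.** **1. The plan's own figures reproduce.** Inputs from the Sample size section: geometric mean ratio 0.8, coefficient of variation 0.9, 80% power, α 0.05 (two-sided, from the general considerations).
- Log-scale SD = √ln(1 + 0.9²) = 0.770; difference = |ln 0.8| = 0.223.
- The exact t test needs 189 per arm in each risk group (power 80.2%); 4 × 189 = 756, as stated.
- Allowing 15% loss: 756 / 0.85 gives 890. By risk group, 378 / 0.85 gives 445, made even to 446, and 2 × 446 = 892, as stated.
- Pooled power with 378 per arm is 97.8%, in line with the stated figure of more than 97%.

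No stated sample-size figure is in question.

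**2. The two definitions side by side.**

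| Section | Condition | Stated N |
|---|---|---|
| Primary efficacy analysis | wear at follow-up 1 | about 240 |
| Sensitivity analysis | wear at 1 month and 12 months | about 240 |
| Study variables (planned 1-month sample) | wear at follow-up 1 | about 240 |

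If the second row is a true both-visits set, its size is 240 × (1 − loss):
- 5% loss (assumed): 228
- 10% loss (assumed): 216
- 15% loss (the SAP's upper allowance): 204, so 36 people's 1-month SEDs are unused

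The 36 is a ceiling. The 15% covers all incomplete follow-up at 12 months, including people lost before the 1-month visit, who could not be among the 1-month wearers.

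**3. Effect on precision.** At 15% loss the standard error grows by √(240/204) = 1.085, about 8%. For a single-visit contrast with equal arms, pooled over risk groups and without baseline adjustment, power for a ratio of 0.8 is Φ(0.223 / SE − 1.960), with SE = 0.770 × √(2/n per arm):
- 120 per arm: SE = 0.0994, power 61%
- 102 per arm: SE = 0.1079, power 54%

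Baseline adjustment would raise both figures by an amount that the SAP gives no correlation to compute.

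**4. Is a 1-month contrast named?** The repeated-measures model is given the overall effect. The graph over time is descriptive. The three-time-point rule could reach time-specific dosimeter outcomes but does not name them, and the contrast stated in that section is at 12 months. So no section names a 1-month between-arm contrast for SEDs.

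**The case against.** The strongest reply is that the wording in the Sensitivity analysis section only lists the subgroup's scheduled visits. Everyone is due to wear the dosimeter at 12 months, the other section imposes no such condition, and the number stays at about 240 where a real completer set would be smaller. No sentence says that withdrawers' 1-month SEDs will be discarded. This reading is plausible and may well be what was meant. It does not remove the need for a correction, because a plan published to limit analysis bias should not leave the inclusion of later withdrawers to be decided once the data are seen.

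A reader might infer more than the document supports:
- **That the SAP estimates a short-term effect conditioned on retention.** It does not: the model targets an overall effect and is labelled a sensitivity analysis.
- **That this is the only use of 1-month dosimeter data.** A graph over time is also planned, and the three-time-point rule may apply to time-specific exposure.
- **That withdrawal in the primary result goes unchecked.** The Primary efficacy analysis section says that "the power was adjusted with a conservative loss to follow-up rate of 15" per cent, and it provides multiple imputation under missing at random if 10% or more lack the primary outcome. A 15% loss would trigger it.
- **That a particular bias follows.** Any figure needs the dependence of loss on 1-month SED in each arm, and the SAP does not give that.

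**Conclusion.** The inconsistency is real and limited. One sensitivity analysis has two analysis sets, and the narrower, read literally, selects on 12-month retention for no statistical gain. The most it can cost is about 36 of 240 one-month records and a standard error about 8% larger, taking the SAP's upper allowance of 15% and assuming that every loss falls after the 1-month visit. The cost is nil if the phrase only describes the visit schedule. Separately, the secondary aim of a 1-month effect has no named SED contrast, and this holds under either reading. The documents do not support a claim that intention-to-treat has been broken. The primary 12-month analysis uses neither definition and is unaffected.

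**What to change.** In both the Primary efficacy analysis and Sensitivity analysis sections:

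1. Define the set as all participants in the 1-month dosimeter subgroup with at least one post-baseline SED value, whatever their 12-month status.
2. Specify a mixed model on log SED with a random intercept and with arm, visit, arm-by-visit, baseline log SED and the stratification factors.
3. Report the 1-month and 12-month contrasts separately, each with its 95% confidence interval. At this sample size the 1-month result is better read as an estimate than as a test.

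Extending the model to all randomised participants, with the 1-month value missing by design outside the subgroup, is optional and would be a larger change. The three steps above need only revised wording and one interaction term, with no new data and no new type of model.

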### Technical details

A second review statistician will independently reproduce the primary analyses. The reviewing statistician will have an overview of all the analyses and will check the code, producing tables selected at random as well as any other pieces of code as desired.

## Data Availability

Not applicable

## Abbreviations

CI: Confidence interval
DOSPERT: Domain-specific Risk-taking
F1: Follow-up 1
F2: Follow-up 2
GEE: Generalised estimating equation
GLMM: Generalised linear mixed model
HEAP: Health Economics Analysis Plan
ICH E9: International Conference on Harmonisation, Statistical Principles for Clinical Trials
MAR: Missing at random
MHI-5: Mental Health Inventory
MICRA: Multidimensional Impact of Cancer Risk Assessment
RCT: Randomised controlled trial
SAP: Statistical analysis plan
SD: Standard deviation
SED: Standard Erythemal Dose
UV: Ultraviolet radiation
